## 11.0 DATA PROCESSING

Raw data obtained from the study will be entered into the Statistical Package for Social Sciences (SPSS) software version 19.0. The data will be clean and check for double entry or outliers before performing the analysis. The data input by the researcher.

## 12.0 DATA ANALYSIS

Patient demographic, clinical variables and baseline value will be compare between groups by the use of independent t-test for normally distributed variables and Mann Whitney test for non-normally distributed variables. Chi-square test will be use for discrete variables. The analysis will be done according to the intention-to-treat (ITT) principle. The missing values will be replaced by

the last readings carried forward. General Linear Model repeated measures ANOVA will be conducted to examine the changes overtime within-groups and between-groups. In the repeated measures model, the baseline value of co-morbidities, medication used, smoking and alcohol consumption were used as covariates in analysis for lipid profiles and blood pressure measurements. The outcome results from baseline to follow up at 6 months and 12 months will be presented as mean group differences, 95% confidence interval, p value and partial eta squared. A p-value of  $<0.05$  was considered statistical significant and effect size as proposed by Cohen (1998) were (0.01= small effect, 0.06= moderate effect and 0.14= large effect [65]. All statistical analysis will be performed using the SPSS software version 19.0 (SPSS Inc, 2009, Chicago, Illinois)

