## **5.8 Sample size estimation**

Referring to the study by Kulzer et al [42] using a group based lifestyle intervention study to prevent diabetes mellitus; mean weight loss and duration of physical activity per week were significantly higher while fasting glucose was significantly lower in the intervention group compared to the control group after 12 months follow up. Using the sample size calculation from STATA

program, with power of 80% and significant level preset at 0.05, using different indicators, the calculated sample sizes are as the following:

|                                        | Duration of physical activity (minutes) | Fasting blood glucose (mg/l) | Weight loss (kg) |
|----------------------------------------|-----------------------------------------|------------------------------|------------------|
| Mean difference 1                      | 17.9                                    | 1.8                          | 3.8              |
| Mean difference 2                      | 46.6                                    | -4.3                         | 1.4              |
| Standard deviation 1                   | 63.8                                    | 13.1                         | 5.2              |
| Standard deviation 2                   | 95.5                                    | 11.3                         | 4.1              |
| Calculated Sample size group 1         | 122                                     | 64                           | 60               |
| Calculated Sample size group 2         | 122                                     | 64                           | 60               |
| Final sample size (with 30% attrition) | 122 x 2 = 244                           | 83 x 2 = 166                 | 78 x 2 =156      |

Based on the above, the largest sample size will be used in this proposed study to ensure adequate power for most outcome measures. Therefore, 244 subjects will be require for this study.

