#### **6.4 Outcome measures**

The primary outcome measures for this study are fasting blood glucose, 2-hour plasma glucose and HbA1C. Secondary outcome measures are weight, BMI, waist circumference, Total cholesterol, Triglyceride, LDL cholesterol, HDL cholesterol, Systolic and Diastolic blood pressure, physical activity, diet intake and HRQOL. All these will be taken at baseline, six months and twelve months except for HRQOL that will be measured at baseline and twelve months. The primary assessment time-point of this study is at 6-month to measure the immediate effect of the intervention. The final visit which occurred at 12-month will be used to measure sustainability of the intervention.

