### **13.0 STUDY LIMITATIONS AND MEASURES TO MINIMIZE IT**

- i) Measurement bias can occur while taking recording or taking measurements (i.e.; recording the weight, height, Blood Pressure, waist circumference). The inter-observer variation can be avoided by training of the staffs conducting the measurements and using same type of instruments. The machines or instruments must be calibrated before use.
- ii) Information bias on physical activity and dietary intake recall. This can occur whereby the respondents might not give the true or exact answers to the questions, either they have forgotten or refused to reveal some information to others. Sometimes, the interpretation of questions might be differently interpreted by the respondents. The limitation unfortunately has to be acknowledged.
- iii) Drop out of participants from the study can occur at any time and without reasons. Therefore, measures have to be taken by conducting regular meeting with the partner organizations to discuss about progress and problems encountered. Immediate action should be taken if any

problems arise. The peer-educator formed among the MDA members can help to track the defaulter cases by means of social visit and follow up.

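### Carrying the last reading forward sets early dropouts to zero change at the primary 6-month visit and copies 6-month values into the 12-month visit meant to test sustainability

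*Protocol*

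**What the plan says.** Protocol section 12.0 (Data analysis) commits to a single rule: "The missing values will be replaced by" "the last readings carried forward". The same section says "The analysis will be done according to the intention-to-treat (ITT) principle" and then "General Linear Model repeated measures ANOVA will be conducted to examine the changes overtime within-groups and between-groups". The protocol states no assumption about why values are missing.

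Three other places determine what the rule does:

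- Section 6.4 (Outcome measures): "The primary assessment time-point of this study is at 6-month to measure the immediate effect of the intervention". It adds: "The final visit which occurred at 12-month will be used to measure sustainability of the intervention".
- Section 5.8 (Sample size estimation): the last row of the table is labelled "Final sample size (with 30% attrition".
- Section 13.0 (Study limitations): "Drop out of participants from the study can occur at any time and without reasons".

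Sections 6.4 and 10.0 (Table 8) give three assessments: baseline, 6 months and 12 months. Quality of life is taken only at baseline and 12 months.

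**The concern.** No outcome visit lies between baseline and the primary time point. At 6 months, carrying the last reading forward can therefore only mean carrying baseline forward, so each early dropout enters the primary comparison with a change of exactly zero. For quality of life the same happens at 12 months.

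At 12 months the rule does something different. A participant seen at month 6 and then lost is given the 6-month value again. The final visit exists to show whether the early effect lasts, and for these people the rule supplies the answer.

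At stake are the size of the primary 6-month difference, the coverage of its confidence interval, and whether a finding of sustained effect at 12 months comes from data or from the imputation.

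**Working it through.** **Inputs from section 5.8.** Fasting-glucose mean changes are 1.8 and -4.3 (difference 6.1, units as printed), with SDs 13.1 and 11.3. Significance level is 0.05, power 80%, and the final size 244, or 122 per group. The attrition allowance is 30%.

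**Assumptions, because the protocol does not give them.** The 6.1 comes from a 12-month source result and is assumed to apply at 6 months. Loss is equal in both arms unless stated. Dropouts would have changed like completers. The split of loss by time is varied. The test is a normal approximation to the between-arm comparison of change at one visit.

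**1. The plan's own figure.** The pooled variance is (13.1² + 11.3²)/2 = (171.61 + 127.69)/2 = 149.65. Then n = 2 × (1.96 + 0.8416)² × 149.65 / 6.1² = 63.1, rounded up to 64 per group, as stated. Also 64 × 1.3 = 83.2, against 83 stated. The inputs are read correctly.

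**2. Six months.** With a fraction f0 lost before month 6, the expected difference is (1 - f0) × 6.1.

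- f0 = 0.15: 0.85 × 6.1 = 5.19
- f0 = 0.30: 0.70 × 6.1 = 4.27

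With q = 1 - f0, the variance of change in an arm with mean m is q(SD² + m²) - (qm)².

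- f0 = 0.15: arm variances 146.3 and 110.9; SE = √(257.2/122) = 1.45; bias 0.915/1.45 = 0.63 SE; coverage = Φ(2.59) - Φ(-1.33), about 90%
- f0 = 0.30: arm variances 120.8 and 93.3; SE = √(214.1/122) = 1.32; bias 1.83/1.32 = 1.38 SE; coverage = Φ(3.34) - Φ(-0.58), about 72%

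With unequal early loss the difference is (1 - c) × 1.8 + (1 - t) × 4.3, where c and t are the control and intervention losses. Loss of 10% and 50% gives 1.62 + 2.15 = 3.77. Loss of 50% and 10% gives 0.90 + 3.87 = 4.77.

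**3. Twelve months.** With f6 lost between months 6 and 12, the expected difference is (1 - f0 - f6) × d12 + f6 × 6.1, where d12 is the true 12-month effect.

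*True effect zero* (intervention mean change set to the control arm's 1.8, SDs unchanged):

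- f0 = f6 = 0.15: 0.15 × 6.1 = 0.915; arm variances 146.3 and 113.2; SE 1.46; ratio 0.63; two-sided false-positive rate about 10%
- f6 = 0.30: 0.30 × 6.1 = 1.83; arm variances 171.6 and 135.5; SE 1.59; ratio 1.15; false-positive rate about 21%
- f0 = 0.30, f6 = 0: shown effect 0

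*Half the effect kept* (d12 = 3.05):

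- f6 = 0.30: 6.1 × (0.5 × 0.70 + 0.30) = 3.97, or 65% of the 6-month difference instead of 50%
- f0 = f6 = 0.15: 6.1 × (0.35 + 0.15) = 3.05. The 12-month difference happens to be right, but set against the shrunken 5.19 it reads as 59% retained.

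**4. Power.** At 122 per group and 30% early loss, the ratio of difference to SE is 4.27/1.32 = 3.2 with the rule. It is 6.1/√(299.3/85.4) = 6.1/1.87 = 3.3 in the 70% observed. Power is about 90% either way, so the damage is to the estimate and not to power.

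**The case against.** The strongest defence is that the bias is conditional. If people who leave truly return to baseline, the 6-month rule is unbiased. With the planning means, every 6-month scenario above errs towards no difference. At 12 months, early loss shrinks the effect while later loss preserves it, so the two can offset. All of this stands and limits what can be said about size. It does not rescue the rule, because the protocol neither states nor supports the assumption the rule needs.

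The zero 12-month effect is also extreme. Section 5.8 describes its source result as a 12-month one, and Table 4 keeps group sessions going to month 9 and personal contact to month 12. That is accepted, which is why the half-retained case is shown.

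The 30% is a planning allowance and not a forecast. The physical-activity column that sets the 244 shows 122 × 2 with no inflation, and sections 7.0 and 13.0 plan follow-up of defaulters. Actual loss may be lower.

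An analysis plan not shown here could add sensitivity analyses. But the carry-forward rule is stated in the protocol as the main method, so the point concerns a rule that is fixed, not detail that is absent. A mixed model also rests on an untestable assumption, missing at random. That is true, but it does not write the sustainability conclusion into the data.

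Two stronger readings are tempting and should not be drawn:

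- *That standard errors are too small because imputed values count as observed.* For the 6-month contrast, simulation with these inputs and 30% early loss gave a model SE of 1.32 against a sampling SE of 1.32. The loss of coverage comes from bias.
- *That upward glucose drift with unequal dropout manufactures an effect.* The section 2.3 progression figures are diabetes incidence, not mean glucose change. Selection on the baseline glucose test could equally push values down.

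**Conclusion.** The concern holds as a should-fix. The stated rule fixes a zero change for everyone lost before the primary time point, and it lets 6-month values stand in as evidence at the visit that judges sustainability. Both follow from the visit schedule and need no assumption.

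The sizes do need assumptions: a difference of 6.1 at 6 months, equal loss, and dropouts who resemble completers. On that basis the primary difference is understated by 15% to 30% when early loss is 15% to 30%. Apparent retention is overstated whenever the effect fades and some loss falls after month 6. A reader might infer that the trial's result is bound to be biased by these amounts or in a known direction. The documents do not support that, since the timing, reasons and arm split of dropout are unknown.

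**What to change.** In section 12.0, replace both the carry-forward rule and the GLM repeated-measures ANOVA as the main analysis. Use a linear mixed model for repeated measures on all observed data, with arm, visit, arm-by-visit interaction, the baseline value, and the covariates section 12.0 already names for lipids and blood pressure. Use an unstructured covariance, no imputation, and everyone analysed in the arm to which they were allocated. Report the 6-month and 12-month contrasts from this model.

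Keep the carry-forward analysis only as a sensitivity analysis. State that the 12-month sustainability conclusion will not rest on carried-forward 6-month values.

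The cost is a change of wording and a little more programming, using the mixed-model procedure in the same SPSS package, with no new data or participants. The downsides are reliance on missing at random and possibly wider confidence intervals. The change does not address the separate limitation of one community per arm.

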#### **5.0 METHODOLOGY**

##### **5.1 Study design**

This is a Quasi-experimental study with repeated measures, collaboration between Department between the research team from Department of Social and Preventive Medicine, University of Malaya and community volunteers from Malaysian Diabetes Associations (MDA), local residential committees and primary health clinics.

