## 5.2 Study area

The study will be conducted in two sub-urban communities in Seremban, Negeri Sembilan, Malaysia. Based on 2010 report [33-35], two communities i.e., Ampangan and Senawang with similar demographic and socioeconomic characteristics were selected.

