## **5.6 Allocation of participants**

The study participants will be allocated to the intervention or control group depending on which community they were enrolled at the time of the baseline screening.

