## **5.10 Case definition**

### **i) Inclusion criteria**

Participants are eligible if they live or work within the community area, age between 18- 65 years old, able to read and understand Bahasa Malaysia or English language, are at risk of type 2 diabetes with fasting blood glucose concentration of between 5.6 to 6.9 mmol/L, and/ or 2-hour 75 g oral glucose tolerance test concentration of between 7.8 mmol/L and 11.0 mmol/L [19], Body mass index (BMI) of between 23-39 kg/m^2 and had no contraindications to participate in weight management program or physical activity.

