## 8.0 STUDY VARIABLES

| Independent variables |                            | Dependent variables                                                         |
|-----------------------|----------------------------|-----------------------------------------------------------------------------|
| i.                    | Age                        | a) Changes in Weight (kg)                                                   |
| ii.                   | Gender                     | b) Changes in Body Mass Index (kg/m  )                          |
| iii.                  | Ethnic group               | c) Changes in waist circumference (cm)                                      |
| iv.                   | Education level            | a) Changes in fasting plasma glucose (mmol/L),
2hPG (mmol/L) and HbA1C % |
| v.                    | Socio-economic status      | b) Changes in TC, HDL, LDL, TG (mmol/L)                                     |
| vi.                   | Family history of Diabetes | c) Change in SBP and DBP (mmHg)                                             |
| vii.                  | History of smoking         |                                                                             |
| viii.                 | History of alcohol intake  |                                                                             |

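### Arms are two non-randomised communities, yet section 12 adjusts only lipids and blood pressure, leaving the three primary glycaemic outcomes without confounder adjustment

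*Protocol*

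**What the plan says.** Section 5.1 describes the design: "This is a Quasi-experimental study with repeated measures". Section 5.2 names two sites: "two communities i.e., Ampangan and Senawang with similar demographic and socioeconomic characteristics were selected". Under section 5.6 participants are "allocated to the intervention or control group depending on which community they were enrolled at the time of the baseline screening". Each arm is therefore one community.

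Section 6.4 states: "The primary outcome measures for this study are fasting blood glucose, 2-hour plasma glucose and HbA1C". It adds: "The primary assessment time-point of this study is at 6-month". Lipids and blood pressure are secondary there.

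Section 12 specifies repeated-measures ANOVA for changes within and between groups. Its only covariate sentence lists co-morbidities and medication and continues: "smoking and alcohol consumption were used as covariates in analysis for lipid profiles and blood pressure measurements". Baseline characteristics are tested between groups, but no adjustment rule follows from those tests.

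Section 8 lists eight independent variables: age, gender, ethnic group, education, socio-economic status, "Family history of Diabetes", smoking and alcohol. Table 8 places socio-demography at screening and BMI at baseline. Section 13 discusses measurement bias, information bias and drop-out, but not confounding by community.

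**The concern.** Without randomisation, the two groups may differ in ways that affect how glucose changes over six months. The protocol lists the obvious candidates as study variables, and it applies some adjustment to secondary outcomes. It gives the primary outcomes none. A difference in glucose change that comes from the mix of volunteers in each community would then be reported as an effect of the programme, and the trial's main conclusion rests on that comparison.

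The test itself is also left open. In a repeated-measures ANOVA the group-by-time term compares changes, while the between-group main effect averages levels over all visits, baseline included. The main effect would carry any standing difference between the communities straight into the result.

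**Working it through.** **Inputs.** The fasting glucose column of the sample size table (section 5.8) gives mean changes of 1.8 and -4.3, SDs of 13.1 and 11.3, and 64 per group at 80% power and a 0.05 level (taken as two-sided). The planned total is 244, or 122 per arm. With 30% attrition, 122 × 0.70 = 85 per arm. Glucose figures below are in the table's own units.

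**The plan's figure.** n = (SD1² + SD2²)(z₀.₉₇₅ + z₀.₈₀)² / difference² = (171.61 + 127.69) × 7.849 / 6.1² = 63.1, so 64 per group. This reproduces.

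**SD of change.** √((13.1² + 11.3²)/2) = 12.23.

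**Effect of an unremoved confounded difference.** Suppose the intervention does nothing, but the communities differ in mean change by b SD. The test statistic is shifted by b/√(2/n), and the chance of p < 0.05 is Φ(-1.96 + shift) + Φ(-1.96 - shift).

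| b (assumed) | Glucose units | Share of planned 6.1 | Shift, 85 / 122 per arm | False-positive rate, 85 / 122 per arm |
|---|---|---|---|---|
| 0 | 0 | 0% | 0 / 0 | 5% / 5% |
| 0.1 | 1.22 | 20% | 0.65 / 0.78 | 10% / 12% |
| 0.2 | 2.45 | 40% | 1.30 / 1.56 | 26% / 35% |

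**How such a b could arise.** For a single confounder, b is its correlation with glucose change times its imbalance in SD units. Assumed imbalances of 0.2 to 0.5 SD with correlations of 0.1 to 0.5 give b from 0.02 to 0.25. At 122 per arm that is 0.24 to 3.06 glucose units and a false-positive rate of 5.3% to 49.7%. The low end is harmless and the high end is not, and the documents do not say where this trial lies.

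**What the baseline measurement already removes.** In a simulation of change from baseline at 122 per arm, a constant level difference of 0.5 between communities left the error rate at 5%. A confounder imbalanced by 0.5 SD that acts on change raised it to about 20% (slope 0.3) and 43% (slope 0.5). The exposure is to differences in change, provided the group-by-time term is the test.

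**Choice of adjusted model.** If the communities differ stably by d, a model of the follow-up value adjusted for its own baseline is biased by (1 - ρ)d, where ρ is the baseline-to-follow-up correlation. A change analysis is not. Assume d = 0.2 SD of the outcome and ρ = 0.5. The bias is then 0.1 SD, the standard error is √(1 - 0.25) × √(2/n), and the shift is 0.75 (85 per arm) or 0.90 (122 per arm). The false-positive rates are about 12% and 15%. Baseline adjustment alone is therefore not a safe primary repair here.

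**The case against.** Much can be said for the plan. The communities were chosen for similarity (section 5.2), both arms share the same glucose, BMI and age limits (section 5.10), and each person's baseline is in the model. A full covariate list is often left to a statistical analysis plan.

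These points stand in part. A reader might infer that every community difference would pass for a treatment effect, or that covariate adjustment is the only protection. The documents do not support either reading, because matching, common eligibility limits and the baseline measure all give some protection. That protection is incomplete. Similarity of two areas does not make their volunteers similar, and section 5.5 recruits through halls, mosques, media and healthcare providers. Nor is this only an omission left to a later document: section 12 itself names covariates and confines them to secondary outcomes.

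A reader might also infer that regression to the mean distorts every primary change because baseline readings determine entry. HbA1C is not a qualifying reading, and a person may qualify on only one of the two glucose measures, so that is too broad.

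Finally, since section 5.10 says "Participants are eligible if they live or work within the community area", a reader might infer that people with ties to both communities dilute the effect by a calculable amount. The documents give no number of such people. The group sessions go to the enrolled intervention group, so working nearby does not by itself deliver them. Assigning arms by home address would leave someone who only works in a study community eligible but without an arm.

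**Conclusion.** The point holds in this form. In a comparison of one community with another, section 12 gives the primary glycaemic outcomes no confounder adjustment, although it adjusts some secondary outcomes and section 8 lists the variables. It also leaves the tested term unnamed.

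The size cannot be derived from the documents. The rates of 10-12% at 0.1 SD and 26-35% at 0.2 SD rest on assumed imbalances, a two-sided 0.05 test, the fasting glucose SD from section 5.8, and 85 to 122 per arm. They show that modest confounding would matter in a trial with 90% to 97% power for the planned fasting glucose difference. They do not show that such confounding exists.

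A reader might take adjustment as a cure. With one community per arm it reduces measured individual-level confounding only, and anything specific to the community stays inseparable from the intervention.

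**What to change.** In section 12, for fasting glucose, 2-hour glucose and HbA1C:

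- Name the between-group difference in change from baseline to 6 months (the group-by-time contrast) as the test.
- Adjust it for age, gender, ethnic group, education, socio-economic status, family history of diabetes, smoking, alcohol and baseline BMI. Fix this list in advance and do not select from it by baseline p-values.
- Report two sensitivity analyses alongside it: the 6-month value adjusted for its own baseline plus the same covariates, and the unadjusted change. Say beforehand that change-score and baseline-adjusted answers can differ when the communities differ at baseline.

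In section 13, add that with one community per arm, adjustment reduces measured individual-level confounding but cannot separate community from intervention.

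The cost is slightly more analysis work and possibly differing estimates to report and explain. The covariates are already study variables or baseline measurements, so no new data or visits are needed.
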